**Figure 1 fig1:**
[figure not shown]
Specification of the study device.

## Outcomes

The main outcome of interest is mean change in ADAS-Cog scores from baseline to Week 12 between groups. ADAS-Cog is the *de facto* standard scale developed for assessing anti-dementia treatment. Other outcomes include global function, assessed by Clinical Dementia Rating scale; quality of life, evaluated by the DEMQOL (23) and DEMQOL-proxy (24); cognition, measured by the MMSE (with a score range of 15 to 30); global impression, rated by Participant’s Global Impression of Improvement (PGI-I) and Clinical Global Impression of Improvement (CGI-I); behavioral and psychological symptoms, monitored by Neuropsychiatric Inventory Questionnaire (NPI (25)); and caregivers’ burden, measured by Zarit’s Burden Interview (ZBI (26)). A specialized psychologist, who was blind to group assignment, scored all these outcomes except DEMQOL, DEMQOL-proxy, PGI-I, NPI and ZBI after a clinical interview. The psychologists conducted the assessments at baseline, Week 12, and the follow-up. The psychological evaluations at Week 12 and the follow-up had a 2 week window, respectively. Figure 2 summarizes the schedule for enrolment, intervention, and assessment. We will record any history of substance use disorder, dementia, psychiatric disorders, neurological disorders, brain injury and other conditions at baseline to exclude patients with clinically contraindicated conditions. Adverse events are any undesirable patient experience during PBM administration. We will monitor and record all adverse events throughout the study via self-report or clinical observations, regardless of causal relationship. We will follow up any untreatable adverse events after trial completion. The principal investigator will diagnose, treat, and explain any serious adverse events to the relevant patients. The subinvestigators will also report any information related to such adverse events to the principal investigator. The principal investigator is responsible for reporting any serious adverse events to the relevant authorities, including the clinical research review board, the Ministry of Health, Labour, and Welfare, and the pharmaceutical and medical device agencies.

**Figure 2 fig2:**
[figure not shown]
The schedule of this study. The time point of post-tDCS evaluation will be allowed within ±7 days and that of follow-up evaluation will be allowed within 14 days. ADAS-Cog, Alzheimer’s Disease Assessment Scale-Cognitive Subscale; ADL, activities of daily living; AL, allocation; BL, baseline; CDR, Clinical Dementia Rating; CGI-I, Clinical Global Impression-Improvement; FU, follow-up; GDS, geriatric depression scale; MMSE, Mini-Mental State Exam; NPI, Neuropsychiatric Inventory; PBM, photobiomodulation; Q’re, questionnaire; ZBI, Zarit Burden Interview.

Serious adverse events are any undesirable medical occurrences at any dose that: (1) Cause death. (2) Pose a threat to life. (3) Necessitate inpatient hospitalisation or prolong existing hospitalisation. (4) Lead to persistent or significant disability/incapacity. (5) Are congenital anomalies/birth defects. (6) Require interventions to prevent permanent impairment damage. The psychiatrists involved in the treatment will document the name, occurrence date, severity, grade, intervention implemented (if any), outcome and relationship to the study medication in an electronic clinical research form (eCRF). Any symptoms that were present at baseline and did not worsen during the study will not be considered as adverse events. Adverse events are classified into three categories in this study: Mild: asymptomatic or mild symptoms; clinical or diagnostic observations only; no intervention required; no impact on usual daily activities. Moderate: minimal, local or non-invasive intervention required; limiting age-appropriate instrumental activities of daily living (ADL); some impact on usual daily activities. Severe: medically significant, life-threatening or related to death; hospitalisation or the prolongation of hospitalisation required; disabling; limiting self-care in ADL; significant impact on usual daily activities.

### Sample size calculation

We aim to enroll 30 participants. In Chao’s et al. report (19), the intervention group scored 32.3 ± 4.8 and the control group scored 39.2 ± 2.6 on ADAS-Cog, which is an efficacy evaluation item for cognitive function. In this trial, assuming a 1:2 allocation ratio of sham stimulation group to real stimulation group, an ADAS-Cog score of 39.2 for the sham stimulation group, an ADAS-Cog score of 32.3 for the real stimulation group, a standard deviation of 4.8, *α* = 0.05, and a power of 0.80, the required sample size was calculated to be 18 (6 for the sham stimulation group and 12 for the real stimulation group) using https://clincalc.com/stats/samplesize.aspx. Considering that this study includes patients with mild cognitive impairment, which is a preliminary stage of the previous study, and that the ADAS-Cog score may decrease overall, we multiplied the sample size by 1.5 to obtain 27, and further considered adherence and dropout cases to obtain 30.

### Sequence generation

We will use a computer-generated stratified sequence from the Mujinwari system^2^ to assign participants to the active or sham PBM group in a 2:1 ratio. Our custom electronic data capture (EDC) system, based on Google Workspace For Business (Google, United States), will collect all data. A cloud computer will keep group assignment and other personal identification data. It will ensure a balanced distribution of diagnosis types (e.g., major neurocognitive disorder or mild neurocognitive disorder). This randomisation method stratifies by diagnosis, and the independent personnel can access the allocation results and provide the appropriate device. The principal investigator and subinvestigators can access each participant’s allocation and disclose it to the participants and raters only after the complete study data is consolidated.

### Data research topic methods and data management

To evaluate the intervention, we will perform assessments by clinicians at baseline and Week 12 (Figure 2). Experienced psychologists unaware of the group allocations will conduct the baseline, Week 12 and follow-up evaluations. Participants and study partners will complete scheduled questionnaires and report adverse events between these visits. All data, except for the informed consent document, will be entered into the EDC anonymously and verified by independent data managers. Considering the device’s safety and the blindness of study personnel, we will not composite the specific data monitoring committee, but data monitors will oversee and review the trial progress. Participants can withdraw their consent or discontinue participating in the study at any time, but we will collect data as much as possible unless consent is withdrawn, or it is at least a serious deviation from the protocol. We will terminate the intervention if we observe any serious adverse events (SAEs). The following auditing standards for field work apply to this study based on the Clinical Research Act: audits will be conducted if any of the following criteria are met: (1) at least two SAEs that are causally related to the medical device are reported; (2) at least two serious protocol deviations are detected; (3) multicentre clinical trials are initiated; or (4) potential severe conflicts of interest that deviate from the prespecified plan for conflicts of interest are identified. We will report any necessary protocol amendments and their outcomes to both the clinical research review board and the Ministry of Health, Labour, and Welfare for registration on the Japan Registry of clinical trials website. After completing the trial, we will publish an original article to disseminate the data results.

### Statistical analysis

We define two populations for our analyses. Full Analysis Set (FAS) will be those participants who are randomised and observed for efficacy assessment after taking active or sham devices home; Safety Analysis Set will be those who are randomised and observed for any safety assessment. Our primary analysis for efficacy will be FAS. Our primary analysis will be intention-to-treat and include all randomised patients in the active or sham group, and we will report their demographic characteristics. We will also perform per-protocol set analysis after excluding cases with protocol deviations as sensitivity analyses. To estimate the mean treatment effect, we will use a linear model for analysis of covariance (ANCOVA) to detect changes in ADAS-Cog, MMSE, CDR, PGI-I, CGI-I, DEMQOL, DEMQOL-Proxy, NPI, and ZBI as secondary outcomes at baseline and Week 12. The ANCOVA will incorporate the covariates of group, baseline score of each outcome and disease (mild cognitive impairment or dementia), which are the stratification factors of dynamic allocation. We will not plan any interim analyses. The primary statistical test will be a *t*-test for the difference of the adjusted means of ADAS-Cog between the groups at Week 12. We will also conduct *t*-tests for the follow-up period and/or the other outcomes. For missing data, we will impute the baseline score as a sensitivity analysis. We will use a Fisher’s exact test to assess the blinding integrity. Additionally, we will describe the demographic characteristics of the patients and compare them between the two groups using a two-sample *t*-test or Fisher’s exact test. We will also examine the correlations between the baseline characteristics, ADAS-Cog, MMSE, CDR, DEMQOL, DEMQOL-proxy, NPI-Q, and ZBI and the cognitive outcomes at Week 12 and follow-up. We will use SAS V.9.4 or later for the statistical analysis. The results will be significant at *p* < 0.05 and statistical tests will be conducted for two-tailed hypotheses.

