Both devices will have a green light indicator and will turn off automatically after 20 min. The participants and their study partners are taught to do PBM at their home or wherever comfortable three times a week within the same range of a day (morning, afternoon, or evening). They will be unable to discern whether they are using the active or sham device. The assessors and participants will be blinded to the treatment allocation to enhance the study validity. At the end of Week 12, the participants will be asked to guess their treatment group to assess the blinding quality. The participants and their study partners will also monitor and report any adverse events to the researchers remotely, as well as submit periodic reports of efficacy, safety, and satisfaction. The study partners will keep track of the device usage frequency and occasionally contact the participants or their partners to encourage adherence to the study protocol.

Any changes in the concomitant therapy of the participants, such as starting, stopping, or adjusting the dose, should be documented, and reported to the researcher. The researcher will train the patient and study partner on operating the device at home and provide written instructions before the first use. The researcher will also verify that the patient and study partner can use the device correctly. A video tutorial is available for reference at any time, and any issues or questions regarding the device use are regularly monitored to enhance adherence. The participant will be withdrawn from the study if any of the following conditions apply, as determined by the principal investigator or subinvestigators when the participant revokes their consent or asks to stop participating in the research; the participant is affected by a disease outbreak or a pandemic; the device shows insufficient efficacy for the participant; the participant fails to attend the evaluation and cannot be reached; the principal investigator or subinvestigators judge that the participant’s mental and physical burden is too high to continue in this study; there is a serious breach or violation of the research protocol. The entire study may be terminated by the Independent Safety and Effectiveness Committee, which convenes when three or more serious adverse events related to the study device occur.

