## Discussion

Since dementia is a condition that involves insidious deterioration of cognitive and social functioning, the long-term effects of certain intervention should be clinically important. Thus, we should conduct a long-term trial with minimizing number of visits in hospitals to enhance adherence to the intervention. To this end, this device is suitable for home use, convenient and proper to wear or remove it. Besides applications at home needs fundamental safety of the device. This device has gained the status of General Wellness Device from the US Food and Drug Administration due to the safety and ability of home use. The remaining problem is the resource to conduct a huge clinical trial with long-term duration. Most other studies cannot overcome this and PBM studies have limited sample size generally. This study also fell to prey but the positive results of the properly conducted study hopefully evoke further and bigger clinical studies.

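### The only stated missing-data sensitivity analysis sets every missing change to zero, so its agreement with the primary result would not show robustness

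*Protocol article*

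**What the plan says.** The Statistical analysis section gives one rule for missing outcomes: "For missing data, we will impute the baseline score as a sensitivity analysis". The only other sensitivity analysis is this: "We will also perform per-protocol set analysis after excluding cases with protocol deviations as sensitivity analyses". That one removes participants and does not deal with missing scores.

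The primary test is a t-test "for the difference of the adjusted means of ADAS-Cog between the groups at Week 12", from an ANCOVA with group, baseline score and diagnosis. The section describes the primary population in two ways: "Full Analysis Set (FAS) will be those participants who are randomised and observed for efficacy assessment after taking active or sham devices home" and "Our primary analysis will be intention-to-treat and include all randomised patients in the active or sham group".

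Two other statements bear on who might be missing. The Discussion says that "dementia is a condition that involves insidious deterioration of cognitive and social functioning". The Intervention section lists among the reasons for withdrawal that "the device shows insufficient efficacy for the participant". Against this, the data management section undertakes to go on collecting data after discontinuation, except where consent is withdrawn or there is a serious deviation.

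**The concern.** A missing-data sensitivity analysis should show whether the conclusion survives if those who were lost did worse than the primary analysis assumes. Filling in the baseline score cannot show this. It gives each lost participant a change of exactly zero, which flatters anyone who declined and penalises anyone who improved. The article itself gives reasons to expect that some of those lost will have declined.

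The filled-in scores are also analysed as if they had been measured, so the standard error makes no allowance for the lost information.

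At stake is how the result is read. With 30 participants, two or three losses matter. If the baseline-imputed result agrees with the primary one, readers may take the finding as robust when the relevant assumption was never tested.

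**Working it through.** **The plan's own figures.** The sample size section uses a difference of 39.2 - 32.3 = 6.9, SD 4.8, two-sided α 0.05, power 0.80 and two active per sham.

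- Sham n = (1 + 1/2) × (1.960 + 0.842)² × 4.8² / 6.9² = 1.5 × 7.85 × 23.04 / 47.61 = 5.70, rounded up to 6. With 12 active the total is 18, as stated.
- 18 × 1.5 = 27, and 27 / 0.90 = 30. The step to 30 would fit about 10% loss (3 people), although the article gives no rate.

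**Inputs for the check.** From the article: 20 active, 10 sham, SD 4.8. Assumed: the SD applies to change (the article attaches it to group scores), sham change of +1 point over 12 weeks (range 0 to +2 in A; no rate is given), and the loss rules below. The test is an unadjusted t-test on change, because no baseline correlation is given for the ANCOVA. Higher scores are worse, so negative bias favours active.

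**A. No true effect; half of the active participants who worsen by more than 4 points are lost; sham complete.**

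- P(change > 4) = 1 - Φ((4 - 1)/4.8) = 1 - Φ(0.625) = 0.266. Share lost = 0.133, or about 2.7 of 20.
- Mean change of those lost = 1 + 4.8 × φ(0.625)/0.266 = 1 + 4.8 × 0.328/0.266 = 6.92.
- Baseline imputation: bias = -0.133 × 6.92 = -0.92.
- Observed case: active mean = (1 - 0.92)/0.867 = 0.09, so bias = 0.09 - 1 = -0.91.
- Simulated type I error: about 8% observed case and about 10% baseline imputation, against a nominal 5%.

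The same formulas for other assumed declines:

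| Sham change | Observed case | Baseline imputation |
|---|---|---|
| 0 | -0.75 | -0.68 |
| +1 | -0.91 | -0.92 |
| +2 | -1.06 | -1.22 |

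**B. No true effect; the same loss rule in both arms.** Both arm means shift equally, so the bias is about 0 and type I error about 5% for both methods. If only sham decliners are lost, the bias in A changes sign and runs against active.

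**C. True effect present; random 10% loss in both arms.** Baseline imputation multiplies the effect by 0.90.

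- Assumed effect -5.6: 0.90 × -5.6 = -5.04, a shrinkage of 0.56.
- Planned effect -6.9: 0.90 × -6.9 = -6.21, a shrinkage of 0.69.
- Observed case is unbiased in both.

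**D. Planned effect -6.9; 20% of active lost because they worsen.** In simulation (sham change 0 to +3) the observed-case bias is about -1.1 to -1.2 and the baseline-imputation bias -0.2 to +0.5. The two methods part company here.

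**Standard error.**

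- Complete data: 4.8 × √(1/20 + 1/10) = 1.86.
- Random 10% loss, observed case (18 and 9): 4.8 × √(1/18 + 1/9) = 1.96.
- Random 10% loss, baseline imputation, no effect, change +1: the filled-in SD is √(0.9 × 4.8² + 0.9 × 0.1 × 1²) = √20.83 = 4.56, so SE = 4.56 × √(1/20 + 1/10) = 1.77.

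Losing 3 of 30 participants therefore makes the reported SE smaller than if nobody had been lost. In scenario A the simulated mean SE is 1.66, against about 1.85 with complete data.

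**The case against.** A reader might infer more: that baseline imputation shares the bias of a complete-case primary analysis and so gives false reassurance. The case against that reading is strong, in four respects.

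- **Direction.** The biases coincide in favour of active only when decliners leave mainly the active arm and the true effect is nil or small. Nothing in the article says they would. The insufficient-efficacy rule applies to both arms, participants and assessors are blinded, and if the device works more such loss would be expected on sham. In B neither method is biased; in C baseline imputation is conservative and the observed-case analysis is not biased. At -6.9, the loss rule in A removes so few active participants that either bias is only about -0.1.
- **Primary analysis.** The article never calls it complete-case. That is an inference from the full analysis set wording and the single Week 12 ANCOVA, and the same section also says that all randomised participants are included. An unseen analysis plan may settle it.
- **Amount of loss.** Continued data collection after discontinuation should limit it, and the allowance in the sample size would fit only about three people.
- **Remedy.** Multiple imputation with many auxiliary variables and about 10 sham participants could be unstable.

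All four stand and limit the claim. None of them makes baseline imputation an informative check: a method whose error changes sign with unknown loss patterns cannot confirm another result. Nor is this a detail left to another document, since the article itself fixes the method.

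**Conclusion.** The point holds in a limited form. The one stated missing-data sensitivity analysis does not examine worsening among those lost, and it makes no allowance for the lost information in its standard error. Agreement with the primary result would therefore not show robustness.

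The size depends on assumptions the article cannot settle: about -0.9 points with type I error near 10% in the unfavourable case A, nothing in B, and a loss of about 0.6 to 0.7 points of real effect in C. All of these rest on the assumed decline, the assumed loss patterns, SD 4.8 for change and an unadjusted test. The documents do not support saying that the method always errs with the primary analysis, or that it generally favours active treatment. The primary test itself is not shown to be wrong. This is a change that should be made to a supporting analysis.

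**What to change.** Replace baseline imputation as the main missing-data sensitivity analysis. Suggested wording: *Missing Week 12 ADAS-Cog scores will be multiply imputed from a model with group, baseline ADAS-Cog and diagnosis. Imputed values in the active arm will then be worsened in fixed steps, the ANCOVA repeated at each step, and the step at which significance is lost reported.*

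- Add the remotely collected questionnaires as auxiliary variables only if the model stays stable with about 10 sham participants.
- Keep baseline imputation, if wanted, as a labelled supplement.

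The result is easy to read: with 2 of 20 active scores imputed, each point of worsening moves the active mean by 2/20 = 0.1 points, so readers can judge whether the tipping step is plausible.

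The cost is a short change of text, some extra programming in the SAS version already planned, and slightly wider intervals than baseline imputation gives. No further data are needed.

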## Discussion

Since dementia is a condition that involves insidious deterioration of cognitive and social functioning, the long-term effects of certain intervention should be clinically important. Thus, we should conduct a long-term trial with minimizing number of visits in hospitals to enhance adherence to the intervention. To this end, this device is suitable for home use, convenient and proper to wear or remove it. Besides applications at home needs fundamental safety of the device. This device has gained the status of General Wellness Device from the US Food and Drug Administration due to the safety and ability of home use. The remaining problem is the resource to conduct a huge clinical trial with long-term duration. Most other studies cannot overcome this and PBM studies have limited sample size generally. This study also fell to prey but the positive results of the properly conducted study hopefully evoke further and bigger clinical studies.

### Strengths and limitations of this study

This study has several strengths, such as its rigorous sample size estimation for cognitive outcomes based on prior evidence, in contrast to many previous studies that did not perform adequate power calculations. Moreover, the device used in this study is unique in its ability to deliver near-infrared light through the nasal cavity. Given the long duration of 12 weeks for the participants and their caregivers, we implemented strategies to enhance adherence, such as minimizing the number of hospital visits and providing immediate contact with the researchers. The use of remote visits also improved the experience of the researchers. However, we also acknowledge some limitations of this study. First, the study is conducted at a single site, which may affect the generalizability of the findings. Second, the long-term effects of PBM on cognition cannot be evaluated. This is a common challenge in trials of anti-amyloid therapies, which require 78 weeks or more to show results and are still controversial regarding their sustained efficacy. Therefore, the optimal duration of PBM intervention remains an open question.

